## Abstract

**Background:**

Reducing sugar-sweetened beverage (SSB) consumption is a promising dietary target for childhood obesity prevention. This paper describes the design and methods of a cluster randomized trial of H_2_GO!, a youth empowerment intervention to prevent childhood obesity through reducing SSB consumption among a low-income, ethnically diverse sample of youth.

**Methods:**

This cluster randomized controlled trial is an academic-community partnership with the Massachusetts Alliance of Boys and Girls Clubs (BGC). Ten BGC sites will be randomly assigned to the H_2_GO! intervention or a wait-list, usual care control. Eligible study participants will be *N* = 450 parent-child pairs (youth ages 9–12 years and their parents/caregivers) recruited from participating BGCs. The 6-week in-person H_2_GO! intervention consists of 12 group-based sessions delivered by BGC staff and youth-led activities. An innovative feature of the intervention is the development of youth-produced narratives as a strategy to facilitate youth empowerment and parental engagement. Child outcomes include measured body mass index z scores (zBMI), beverage intake, and youth empowerment. Parent outcomes include beverage intake and availability of SSBs at home. Outcomes will be measured at baseline and at 2, 6, and 12 months. With a 75% retention rate, the study is powered to detect a minimum group difference of 0.1 zBMI units over 12 months.

**Discussion:**

Empowering youth may be a promising intervention approach to prevent childhood obesity through reducing SSB consumption. This intervention was designed to be delivered through BGCs and is hypothesized to be efficacious, relevant, and acceptable for the target population of low-income and ethnically diverse youth.

**Trial registration:**

ClinicalTrials.gov NCT04265794. Registered 11 February 2020.

**Supplementary Information:**

The online version contains supplementary material available at 10.1186/s12889-021-11660-5.

## Background

Over one third of U.S. school-age children are overweight or obese [1, 2] and at risk for diabetes, heart disease, and shorter life expectancies [3]. Reducing sugar-sweetened beverage (SSB) intake is a high-impact dietary target for obesity prevention, particularly among low-income youth and youth of color who have persistently higher SSB intake and obesity risk [4–6]. Data from the 2013–2014 National Health and Nutrition Examination Survey (NHANES) indicate that 63.5% of youth ages 6–11 years consumed ≥1 SSBs on a given day [7], with considerably higher SSB intake among low-income youth and Hispanic and non-Hispanic Black youth [4, 5, 7–9]. Low-income youth are also more likely to be heavy SSB consumers (≥500 kcals/day) than higher-income youth [9, 10]. Reducing SSB intake can lead to 8–11% reduction in energy intake among youth [4, 11–15]. Efficacious strategies to reduce SSB intake are therefore needed, particularly among low-income youth and youth of color who are high SSB consumers.

Empowerment approaches hold potential for catalzying positive behavior change in childhood obesity intervention contexts by building youth’s capacity to affect change in their lives and in the broader community [16, 17]. Empowerment-based health interventions seek to improve health behaviors and outcomes, particularly among low-income populations and communities of color, by helping individuals develop an ecological understanding of health and identify strategies for change that are relevant in the context of their lived experiences [18, 19]. There is growing body of evidence that indicates empowerment may mediate behavior change and obesity-related outcomes among youth [16, 17, 20, 21]. Prior youth empowerment interventions have demonstrated small improvements in diet, physical activity, and BMI among youth [22–24], though few have utilized rigorous study designs or examined empowerment as a mediator of intervention effects.

Cultivating youth narratives or stories is one empowerment strategy that may facilitate empowerment and health behavior change among youth of color [25–28]. Unlike traditional didactic approaches, the development of narratives within an empowerment framework engages youth in a transformative process by recognizing knowledge embedded within their personal stories and encouraging youth to take action [19, 29, 30]. The creation and sharing of narratives thus facilitates empowerment through elaborate message processing and personalization [27]. The use of narratives within other health interventions has shown success in behavior change, including improved diet, among adults [31–35]. Results from our pilot site-randomized study of *N* = 100 parent-child pairs indicated that our narrative-based youth empowerment SSB intervention (H_2_GO!) was associated with 6-month reductions in child zBMI and 6-month reductions in SSB intake and increases in water intake among children and parents [36].

The goals of this study are to test the efficacy of H_2_GO! among an ethnically diverse sample of youth through a cluster randomized controlled trial (parallel group) and measure empowerment as a mediator. We partnered with Massachusetts Allianc of Boys and Girls Clubs of America (BGCs) to develop and pilot test H_2_GO! [37]. BGCs are an ideal partner for this proposal due to their commitment to empowering youth to lead healthy lives and their potential to reach large segments of our target population (4 million school-age youth; 56% low-income) nationally. We hypothesize that child participants in the intervention sites will have reduced zBMI and reduced SSB intake compared to child participants in the comparison sites and that the intervention effect(s) will be mediated by youth empowerment. This paper describes the design and methods for the cluster randomized controlled trial of the H_2_GO! intervention.

## Methods/design

### Theoretical foundation

Our study applies Empowerment Theory (ET) [38] through intervention conceptualization, implementation, and measurement. Youth become empowered (e.g., gain mastery over their lives) as they develop critical consciousness, which occurs as they begin to fully understand the factors that shape their environment and in turn their behavior [39]. ET posits that youth empowerment occurs through three interrelated components or processes: 1) *intrapersonal* (development of youth beliefs, such as confidence and sense of agency to make a difference); 2) *interactional* (cultivation of critical awareness and critical thinking skills to help youth become independent decision makers and create situations aligned with their goals); and 3) *behavioral* (provision of opportunities for youth to practice skills in real life contexts and to take action to produce desired changes in their communities) [17]. Our intervention was developed for early and pre-adolescent youth ages 9–12 years, as children under 9 may not have the concrete operational development [40] needed for skills targeted in an empowerment intervention. The H_2_GO! intervention integrates the three ET processes to target SSB intake among youth through BGC staff-led sessions and youth-led activities (Fig. 1).

**Fig. 1 Fig1:**
[figure not shown]
Intervention Conceptual Model by Empowerment Theory (ET) Processes

### Study setting and population

BGC is a national organization that provides affordable after-school programs for over 4 million school-aged youth (29% White, 27% Black, 24% Latino) across 4300 sites nationwide [41]. BGCs are an ideal community partner for youth empowerment interventions due to their commitment to youth empowerment and health promotion [42–48]. BGC sites will be recruited from the 40 BGC sites in Massachusetts, USA and selected for comparability in enrollment size and ethnic composition.

Parent-child pairs will be screened, recruited, and consented by study staff from participating BGC sites via in-person, phone, or web-based modalities. Study staff will obtain parental permission and verbal assent through three main ways: 1) verbal parental permission and verbal child assent in-person in the BGC setting; 2) verbal parental permission and verbal child assent over the phone using a REDCap form (completed and documented by study staff); and 3) online form using REDCap documenting parental permission and verbal child assent. *Child inclusion criteria are:* ages 9–12 years; current member at the BGC study site; able to understand and communicate in English; able and willing to provide consent; parental/caregiver permission to participate; has access to a wifi-enabled device at home (to allow for study participants to continue with intervention participation in the event the intervention needs to transition to online delivery due to COVID-19); and no medical condition that limits ability to change beverage consumption behaviors. *Parental/caregiver inclusion criteria are:* parent/caregiver to a BGC child member; 18 years or older; able to understand and communicate in English; able and willing to provide consent; and no medical condition that limits ability to change beverage consumption behaviors.

### Study design

This study is an unblinded parallel-group cluster randomized controlled trial with *N* = 10 BGC sites randomized to the intervention or comparison status. Geographic location is used as a stratification variable; sites within each stratum are spaced > 5 miles apart to minimize contamination bias. One site within each stratum will be randomly assigned to the intervention and the other to a wait-list, usual care condition. The randomization will be conducted by the project statistician using computer-generated random numbers. We opted to use a stratified sampling scheme to increase balance of BGC characteristics between study arms and include a representative sample of BGCs to increase generalizability.

After sites are randomized, participants will undergo recruitment and enrollment and complete in-person study assessments at baseline, 2, 6, and 12 months follow-up (see Fig. 2). Comparison group participants will have study assessments scheduled to match the timing of each intervention cycle. To enhance adherence to intervention protocols, the study team will complete intervention fidelity and process measures of intervention sessions using intervention attendance, recruitment, and retention rates, as well as an intervention fidelity checklist to score completion of intervention activities (0 = did not do this activity; 1 = partially completed; 2 = completed) across each of the 12 intervention sessions. The study team will also monitor intervention sessions and provide corrective feedback and ongoing trainings and refresher sessions as needed. Intervention fidelity monitoring and corrective feedback processes will be completed remotely via Zoom when study staff were unable to be present onsite BGC due to COVID-19 restrictions.

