### Recruitment and retention

We will utilize the following participant recruitment approaches previously tested in our pilot study (identify eligible child participants through the BGC electronic enrollment record system and in collaboration with BGC staff), which yielded > 95% recruitment rate in our pilot study. Proposed strategies to retain participants include collecting multiple forms of contact information from parent/caregiver participants at baseline, scheduling pre-determined study assessments at dates/times convenient for participants, providing options for online or phone follow-up assessments, implementing a tracking and reminder system, offering assistance and support for participating in study assessments, using email and social media contact approaches, and providing incentives of $20 gift cards per assessment.

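### Children are recruited and measured at baseline after their club has been randomised in an unblinded trial, with no stated safeguard, so who is approached and who agrees can differ by arm

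*Protocol article*

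**What the plan says.** The Study design section sets out a cluster trial of 10 clubs: "This study is an unblinded parallel-group cluster randomized controlled trial with *N* = 10 BGC sites randomized to the intervention or comparison status". Clubs are paired by geography: "One site within each stratum will be randomly assigned to the intervention and the other to a wait-list, usual care condition". Allocation comes first and enrolment second: "After sites are randomized, participants will undergo recruitment and enrollment", followed by the baseline assessment and those at 2, 6 and 12 months.

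On who finds and enrols the families, Study setting and population says: "Parent-child pairs will be screened, recruited, and consented by study staff from participating BGC sites". Recruitment and retention gives the method, which is to "identify eligible child participants through the BGC electronic enrollment record system and in collaboration with BGC staff". It adds that the approach was used in the pilot, "which yielded > 95% recruitment rate in our pilot study".

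The article describes no masking of recruiters, no eligibility list fixed before randomisation, and no consent or baseline taken before allocation.

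Several features bear on the risk from the other side:
- Comparison families get the programme after the study (Comparison condition).
- The primary outcome is change in zBMI from measured height and weight (Primary outcome).
- Recruitment rates are tracked as a process measure (Study design).
- Analysis is by intention-to-treat, and group imbalances at p < 0.1 are adjusted for (Planned statistical analysis).

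**The concern.** Randomising clubs makes the clubs comparable in expectation. It makes the enrolled children comparable only if the way they are found, approached and consented does not depend on allocation. Here all three steps come after allocation in an unblinded trial. In intervention clubs, the club staff who help identify children are colleagues of those who deliver the sessions, or the same people. Families face different immediate prospects: 12 sessions over 6 weeks in one arm, usual programming with a deferred offer in the other. If more motivated families enter in one arm, a difference in 12-month zBMI change could arise without any effect of the programme.

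This kind of bias does not shrink as more children are enrolled, and the planned analysis works only on those who have entered. Baseline measurement after allocation is a second and lesser exposure. It matters mainly for self-reported beverage intake, where knowing the arm could colour the answers. Measured height and weight are much less open to it.

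**Working it through.** **1. Order of events.** Study design gives randomisation, then recruitment and enrolment, then baseline. No other section describes a different order or a step that would conceal allocation during recruitment. The order is stated. That recruiters and families know the allocation is inferred from the word unblinded.

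**2. What each stated feature can do about it.**
- Intention-to-treat keeps participants in their group after enrolment; the selection happens before.
- Change in zBMI removes a difference in baseline level, but not a difference in expected trajectory.
- Adjustment at p < 0.1 reaches measured covariates only. Family motivation is not among the measures in Table 2; child self-efficacy is at best a proxy and is itself collected after allocation.
- The wait-list narrows the difference in incentive to join, but early access still differs.
- Pairing by geography balances clubs, not the children enrolled within them.
- Tracking recruitment rates may reveal a difference in uptake but does not prevent one.

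**3. The plan's own precision.** Inputs from Statistical approach and power: 5 clubs per arm, 45 pairs per club, 75% retention, SD 0.15, ICC 0.05, α = 0.05 (taken as two-sided).
- Retained per club: 45 × 0.75 = 33.75
- Design effect: 1 + (33.75 − 1) × 0.05 = 2.6375
- Effective n per arm: 5 × 33.75 / 2.6375 = 63.98
- Standard error of the difference: 0.15 × √(2 / 63.98) = 0.0265
- Power for 0.1: 96.5% (normal), 90.8% (t, 8 df), 80.2% (t, 4 df)

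The stated power of over 80% is reproduced and is not in dispute.

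**4. Size of a possible bias.** Bias = (difference between arms in the share of motivated families) × (their better 12-month zBMI trajectory). Both inputs are assumptions; the documents give neither.
- Low: 0.10 × 0.05 = 0.005, which is 5% of the 0.1 target
- High: 0.30 × 0.15 = 0.045, which is 45% of the target

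The upper trajectory value, 0.15, is generous. It exceeds the 0.0 to 0.13 difference that the article cites for randomised SSB interventions over 12 to 18 months.

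**5. What that would do to the test.** With no true effect and a standard error of 0.0265, the two-sided false-positive rate would be:

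| Assumed bias (zBMI) | Bias / SE | Normal | t, 8 df |
|---|---|---|---|
| 0 | 0 | 5.0% | 5.0% |
| 0.005 | 0.19 | 5.4% | 5.3% |
| 0.015 | 0.57 | 8.7% | 7.9% |
| 0.03 | 1.13 | 20.5% | 17.0% |
| 0.045 | 1.70 | 39.6% | 32.2% |

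At the low end the consequence is negligible. At the high end it is serious.

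**The case against.** The strongest reply is that the article describes a largely record-based identification process run by study staff, and reports a pilot recruitment rate above 95%. If that rate is the share consenting among those approached, and if it carries over, refusal is under 5%, and differential consent could hardly produce a gap of 10 points or more. The gap would then have to come from arm-dependent choice of whom to approach, and the article does not say that anyone makes such a choice. The primary outcome is also objective and analysed as change.

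Much of this stands. A reader might infer that club staff pick favourable children, or that families consent knowing their arm. The article says neither: staff collaborate in identifying eligible children, and what families are told before consent is not described. A reader might also infer that the baseline zBMI is compromised, or that the small number of clubs causes the problem. Neither follows. Measured height and weight are little exposed, and this kind of bias does not depend on there being 10 clubs.

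The reply does not close the point. The recruitment rate has no stated denominator, comes from the pilot, and says nothing about how those approached were chosen. With a planned 45 pairs per club, the article does not say that every eligible member is approached. Analysing change leaves a difference in expected trajectory untouched.

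**Conclusion.** The concern holds as a risk, not as demonstrated bias. The order of events and the absence of blinding are stated; knowledge of allocation by recruiters and families is a reasonable inference that nothing in the article contradicts. The stated mitigations lessen the risk without removing it. Its size is unknown. On the assumptions above it spans about 0.005 to 0.045 zBMI, and little weight should go on the upper end, because it needs both a large gap in enrolment and a trajectory difference larger than the cited SSB interventions achieved. The case for acting is that the exposure can be reduced cheaply in the design, whereas selection on unmeasured factors cannot be repaired in the analysis.

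**What to change.** Within each stratum, complete consent and baseline assessment in both clubs, and only then have the project statistician release that stratum's allocation. Initial staff training is remote and can follow release.

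The Study design section refers to intervention cycles, and this order protects only children enrolled before release. For any cycle enrolled afterwards:
- freeze the list of eligible members from the enrolment records before release;
- approach those listed in random order, by the same procedure in both arms;
- report the numbers eligible, approached and consented by arm.

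The change alters no sample-size figure, outcome measure or analysis model. It costs revised protocol wording, some scheduling effort at the clubs, and a short delay between baseline and the first session while staff are trained.

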**Fig. 2 Fig2:**
[figure not shown]
Study Flow Chart

Study protocol and procedures, including adapatations and alternative plans that accommodated for COVID-19 restrictions and guidance for in-person and indoor activities, were approved by the Boston University Medical Center Institutional Review Board (protocol #H-39841). Any important protocol modifications will be communicated and approved by the investigators, the IRB, trial participants, the trial registry, and the study sponsor.

### Intervention development

The H_2_GO! intervention was designed to reduce SSB intake (recommended guideline of 0 SSBs/day) and promote replacing SSBs with water (recommended guideline of 5–8 cups/day) among 9–12 year old youth and their parents. Intervention materials, strategies, format, and content were previously pre-tested and refined based on youth, parent, and staff feedback and study staff observations on intervention feasibility, acceptability, and engagement in our pilot study [36, 37]. To prepare for the event that part or all of the intervention may need to be delivered remotely, the study team developed virtual curriculum content and activities (designed to be delivered via Zoom) to parallel the in-person activities. Study staff will train BGC staff to deliver the intervention through a remote-based initial training followed by quarterly booster sessions; this training will review curriculum and protocols for each intervention session through an intervention manual, provide practice of protocol implementation, and include delivery of feedback during mock sessions.

### Intervention condition

The 6-week intervention consists of 12 group-based weekly in-person sessions (1-h sessions twice a week) delivered by trained BGC program staff to BGC child study participants in the BGC setting during regular BGC hours (after-school on weekdays) and a culminating BGC community open house event for all youth and parent members. Intervention activities consist of three main components mapped onto the three ET processes:
**BGC staff-led health sessions for youth (intrapersonal)**: Youth will participate in weekly group-based interactive health sessions delivered by trained BGC staff. The primary objectives are to decrease SSB intake among youth and to promote water intake. Strategies to lead knowledge, confidence, and skill building activities targeting children’s SSB consumption have been previously pilot-tested in our study population (see Table 1 for session topics).**BGC staff-led narrative sessions for youth (interactional)**: Youth will be guided by BGC staff to produce narratives featuring behavioral messages on beverage intake, applying knowledge and skills acquired from the health sessions. Narrative materials will build upon youth’s lived experiences, consist of youth’s own stories, and be developed by youth through a variety of mediums (e.g., print, audio, video). Staff will use pictorial-based analysis methods (e.g., SHOWed) to guide youth to critically reflect on narratives created [49].**Youth-led activities empowering youth as change agents (behavioral)**: Youth will engage parents in critical dialogues by teaching parents knowledge and skills learned through weekly take-home activities and sharing of narrative materials produced, culminating in a youth-led BGC community event that will include a display of narrative materials through an art gallery format; live youth performances, a viewing of finalized narratives, and youth-led taste tests of non-sweetened beverages.

**Table 1 Tab1:** Sample H_2_GO! Pilot Intervention Session Topics and Activities

Weekly BGC-staff led health sessions *Intrapersonal* (building confidence and skills)	Weekly BGC-staff led narrative sessions *Interactional* (critical thinking)	Weekly youth-led activities *Behavioral* (organized youth action)
1. *Water is Good for You!* (hydration demonstration)	Develop print narratives to promote water intake	Teach parents information and skills learned through parallel weekly parent-child activities Engage parents in critical dialogues on target behavioral messages through weekly sharing of narratives
2. *Re-Think Your Drink* (blinded taste tests of flavored water)	Develop print narratives to encourage non-SSB alternatives	
3. *Find the Facts* (label reading, SSB measuring activity)	Develop print narratives to explain how to identify SSBs	
4. *Explore the Corner Store* (scavenger hunt of SSBs and non-SSBs)	Develop audio narratives to explain how to identify SSBs	
5. *Water, Water, Everywhere* (role play skits to find ways to drink water)	Develop video narratives to find opportunities to drink water	
6. *SSB Triggers* (role play skits to manage SSB triggers	Develop video narratives to manage SSB triggers	
**Culminating youth-led BGC community event featuring display of narratives and flavored water taste tests** *Behavioral* (organized youth action)		

Child participants will also receive a reusable water bottle and a pictorial intervention booklet developed by the research team, which includes intervention activity worksheets, parent-child take-home activities, and beverage consumption tracking and goal-setting sheets. Activity worksheets will be completed by participants during intervention sessions, and parent-child take-home activities will be completed following each session. Sample session topics and activities are summarized in Table 1. Additional details on intervention strategies and intervention session activities have been previously described [36, 37].

